## Abstract

**Background:**

Triple-negative breast cancer (TNBC) comprises a heterogeneous group of diseases which are generally associated with poor prognosis. Up to now, no targeted treatment beyond anti-VEGF therapy has been approved for TNBC and cytotoxic agents remain the mainstay of treatment. Ixazomib is a selective and reversible inhibitor of the proteasome, which has been mainly investigated in the treatment of multiple myeloma. In a preclinical study TNBC cells were treated with the first-generation proteasome inhibitor bortezomib in combination with cisplatin and synergistic efficacy was demonstrated. Clinical data are available for carboplatin plus bortezomib in metastatic ovarian and lung cancers showing remarkable antitumor activity and good tolerability (Mol Cancer 11:26 2012, J Thorac Oncol 4:87–92 2009, J Thorac Oncol 7:1032–1040, 2012). Based on this evidence, the phase I/II MBC-10 trial will evaluate the toxicity profile and efficacy of the second-generation proteasome inhibitor ixazomib in combination with carboplatin in patients with advanced TNBC.

**Methods:**

Patients with metastatic TNBC pretreated with at least one prior line of chemotherapy for advanced disease with a confirmed disease progression and measurable disease according to RECIST criteria 1.1 are eligible for this study. Patients will receive ixazomib in combination with carboplatin on days 1, 8, and 15 in a 28-day cycle. The phase I part of this study utilizes an alternate dose escalation accelerated titration design. After establishing the maximum tolerated dose (MTD), the efficacy and safety of the combination will be further evaluated (phase II, including 41 evaluable patients). All patients will continue on study drugs until disease progression, unacceptable toxicity or discontinuation for any other reason. Primary endpoint of the phase II is overall response rate, secondary endpoints include progression-free survival, safety, and quality of life. This trial is open for patient enrollment since November 2016 in six Austrian cancer centers. Accrual is planned to be completed within 2 years.

**Discussion:**

Based on preclinical and clinical findings an ixazomib and carboplatin combination is thought to be effective in metastatic TNBC patients. The MBC-10 trial is accompanied by a broad biomarker program investigating predictive biomarkers for treatment response and potential resistance mechanisms to the investigational drug combination.

**Trial registration:**

EudraCT Number: 2016–001421-13 received on March 31, 2016, ClinicalTrials.gov Identifier: NCT02993094 first posted on December 15, 2016. This trial was registered prospectively.

## Background

Metastatic breast cancer is still an incurable disease and significantly contributes to worldwide cancer mortality [1]. Prognosis clearly depends on the molecular subtype determined either by immunohistochemistry or molecular assays as well as on proliferation rate as determined by the Ki-67 index. By the introduction of novel endocrine agents, targeted agents and immunotherapy, a substantial progress has been made for both hormone-receptor-positive as well as Her2/neu positive metastatic breast cancers [2], although resistance might still exist either primarily or develop during or after therapy.

Triple-negative breast cancer (TNBC) comprises a heterogeneous group of diseases, defined by the absence of an estrogen receptor, progesterone receptor and HER2 expression. TNBC accounts for approximately 15% of breast cancer cases and is now the subtype with the worst prognosis and novel concepts are urgently needed. No targeted treatment beyond anti-VEGF therapy is approved for TNBC so far and cytotoxic agents are the mainstay for the treatment of the advanced disease. Up to 20% of patients with TNBC harbor a germline BRCA mutation [3]. Recently, the results of the phase III trial OlympiAD comparing olaparib, an oral poly(ADP-ribose) polymerase (PARB) inhibitor with standard chemotherapy in pretreated metastatic breast cancer patients harboring a germline BRCA mutation have been published showing favorable efficacy and safety results for the PARP inhibitor [4]. Therefore, an approved target treatment option for a subset of TNBC patients can be awaited within the next year. Due to a generally aggressive course of disease there is an urgent need for the investigation of novel drugs and drug combinations.

### Rationale for the use of ixazomib in breast cancer

Ixazomib is a selective, potent, and reversible inhibitor of the proteasome, which has been investigated for the treatment of multiple myeloma [5]. In solid tumors, the cytotoxic effect of proteasome inhibitors is thought to be mediated through different mechanisms: (1) Inhibition of the Fanconi Anemia (FA) and BRCA1 DNA repair mechanism [6]. The FA signaling cascade coordinates a complex mechanism consisting of three classical DNA repair systems (homologous recombination, nucleotide excision repair, mutagenic translesion synthesis) in response to DNA damage [7]: Five FA proteins (A, C, E, F, and G) regulate the activation of FANCD2 by monoubiquitination and nuclear foci formation. Activated FANCD2 [8] as well as BRCA1 regulate the DNA repair by homologous recombination [9] and are therefore critical for the function of the Fanconi anemia pathway [7]. In addition, FANCD2 interacts with the MRE11-NBS1-RAD50 complex in the repair of DNA crosslinks [7]. Proteasome inhibitors like bortezomib have been shown to inhibit monoubiquitination and/or nuclear foci formation of FANCD2 thereby causing cellular hypersensitivity to ionized radiation and DNA cross-linking agents like platinum salts [10, 11]. (2) Inhibition of p53 degradation. Inhibition of the ubiquitin-proteasome mediated degradation of p53 [7, 12, 13] as well as of the natural cyclin dependent-kinase inhibitors p21 and p27, induces G1 arrest. (3) Induction of apoptosis by inhibition of the canonical and non-canonical NF-kappa B signaling cascade [12–14].

### Rationale for the use of carboplatin in breast cancer

Carboplatin is a platinum based compound that covalently binds with DNA to form intrastrand crosslinks and changes DNA conformation, therefore affecting DNA replication. Compared to cisplatin, carboplatin has a favorable toxicity profile, particularly with less nephrotoxic and neurotoxic side effects but at the price of an increased hematotoxicity [15].

In metastatic breast cancer single agent carboplatin was investigated in several phase II trials including patients irrespective of breast cancer subtype. Response rates were in the range of 20–35% in treatment-naive patients [16–18]. In patients pretreated with chemotherapy response rates of single-agent carboplatin were modest with ORR of lower than 10% in two small phase II trials including 13 and 14 patients, respectively [18, 19]. In a large randomized phase III trial, carboplatin was compared with docetaxel as first line treatment in patients with TNBC or BRCA1/2 mutation-associated breast cancer [20]. Overall response rate, the primary endpoint of this trial, was 31% (59/188) in the carboplatin group and 36% (67/188) in the taxane group. In a preplanned subgroup analysis, overall response rate in the carboplatin arm was 68% (17/25) in BRCA1/2 germline mutated patients compared to 28% (36/128) in patients without germline BRCA1/2 mutation. Combination regimens with carboplatin plus taxanes, anthracyclines, nucleoside analogues, vinca alkaloids, or targeting therapies like poly-adenosine diphosphate-ribose polymerase (PARP)-inhibitors were more promising [21–23]. Based on several phase II trials with response rates in the range of 17–39% [24–28], the combination of carboplatin plus gemcitabine is a clinically established treatment option for pretreated patients with advanced triple-negative breast cancer.

### Rationale for a combination of ixazomib and carboplatin

In a preclinical study the triple-negative breast cancer cell line 4 T1 was treated with bortezomib alone and in combination with cisplatin. The combination of both drugs led to a higher inhibition of cell growth than each drug alone thus suggesting a synergistic effect [29].

TNBC is a rather heterogeneous group of tumors when analyzed with molecular and immunological tools [30–32]. When analyzed at the molecular level, it is mostly categorized within the so called basal-like subtype [30]. The Total Cancer Genome Atlas (TCGA) network uncovered the heterogeneity of genetic alterations in breast tumors and showed a remarkable similarity of basal-like tumors with serous ovarian cancers [33]. Common features between serous ovarian and basal-like tumors are BRCA1 inactivation, RB1 loss and cyclin E1 amplification, high expression of AKT3, high expression and amplification of MYC, and a high frequency of TP53 mutations. Compared to luminal breast cancers, TNBC also have a reduced DNA repair capability due to a reduced expression of DNA repair genes including nucleotide excision repair, Fanconi Anemia pathways and CHK1 [34]. These particular molecular features might be exploited in novel targeted approaches and simultaneously indicate potential overlapping strategies in the treatment of breast and ovarian cancers, with platinum compounds representing the major backbone of treatment for the latter.

Bortezomib in combination with carboplatin was tested in 15 patients with recurrent ovarian cancer in a phase I trial, showing a remarkable antitumor activity with an overall response rate of 47% (2 CR and 5 PR) [35]. One patient suffered from platinum-resistant disease but achieved a complete remission with this combination. Interestingly, bortezomib decreased the serum level of NF-kB, which is known to be increased by carboplatin, in seven of eight patients with increased NF-kB activity after carboplatin infusion. Re-exposure to carboplatin couldn’t reactivate NF-kB during the following cycle, indicating a lasting effect of bortezomib in this regard.

The combination of bortezomib and carboplatin was also tested in 22 patients with platinum- and taxane-resistant ovarian cancer [36]. In these heavily pretreated patients no objective response was seen, but 44% (8 of 18 evaluable patients) had a stable disease. Based on these data, this drug combination could show efficacy in triple-negative breast cancers, known to be biologically similar to ovarian cancer.

The bortezomib and carboplatin regimen was combined with gemcitabine in a triple drug first line regimen in a phase II trial in patients with advanced non-small cell lung cancer (*n* = 114) [37] and in the same indication in combination with bevacizumab within a phase I/II trial (*n* = 16) [38]. The leading grade 3 and 4 toxicities occurring in more than 15% of patients were thrombocytopenia (63%) and neutropenia (52%) in combination with gemcitabine, and thrombocytopenia (58%), lymphocytopenia (25%), diarrhea (25%), nausea (19%), and vomiting (19%) in combination with bevacizumab. Response rates were 23% in the gemcitabine containing trial and 44% in the bevacizumab containing trial [37, 38].

## Methods

### Study design

The phase I part of this study uses an alternate dose escalation accelerated titration design [39] as outlined in Fig. 1 and Table 1. In the accelerated dose-escalation phase a single-patient cohort per dose level will be enrolled, until one dose limiting toxicity (DLT) or 3 moderate toxicities, as outlined below, are observed during cycle 1, or until dose level 4 is reached. At this dose level the cohort is expanded to three patients and dose escalation reverts to a conventional 3 + 3 escalation design [40]. Dose limiting toxicities (DLTs) are defined as drug related adverse events preventing the administration of the drug combination. Such toxicities are defined as grade 3 or 4 non-hematologic toxicities (excluding alopecia, nausea, emesis, diarrhea), grade 3 or greater nausea and/or emesis despite the use of optimal anti-emetic prophylaxis, grade 3 or greater diarrhea that occurs despite maximal supportive therapy, grade 2 peripheral neuropathy with pain or polyneuropathy greater or equal grade 3, neutropenia grade 4 for more than 7 days, febrile neutropenia grade 3, thrombocytopenia grade 4, or thrombocytopenia grade 3 with bleeding. Moderate toxicities are defined as any grade 2 non-hematologic toxicity excluding alopecia, or any grade 3 hematologic toxicity.

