**Fig. 1 Fig1:**
[figure not shown]
Accelerated titration design of the phase I part of the trial. Illustration of the accelerated titration design of the phase I part of the trial. Each box outlined in bold represents a cohort containing the indicated number of patients treated at a given dose level. Ixazomib will be administrated orally on days 1, 8, and 15 and carboplatin intravenously on days 1, 8, and 15 of a 4-week cycle. Drug dosages per dose level are given on the left side of the graph. DLT = dose-limiting toxicity; AUC = area under the curve

**Table 1 Tab1:** Drug dosages per dose level

Dose level	Ixazomib orally on days 1, 8, 15 every 4 weeks	Carboplatin i.v. on days 1,8 and 15 every 4 weeks
1	3 mg	AUC 1.5
2	3 mg	AUC 2
3	4 mg	AUC 2
4	4 mg	AUC 2.5

AUC = area under the curve

The maximum-administered dose (MAD) is defined as the dose at which DLT or 3 moderate toxicities occur in at least two of six patients treated at that dose level. The dose-level just below the MAD is considered the maximum-tolerated dose (MTD), providing that DLT or 3 moderate toxicities are observed in fewer than two of six treated patients (or fewer than one third if more than six patients will be treated) at that dose level. Determination of MAD and MTD is based on DLT or 3 moderate toxicities observed during the first treatment cycle.

Beginning with the 2nd cycle an intra-patient dose escalation is allowed. This is separate from the alternate dose escalation design of the phase I part. If the nadir ANC was ≥500/mL, the nadir platelet count ≥50,000/mL, and non-hematologic toxicities were grade ≤ 1 in the previous cycle, the current dose level can be escalated by one dose level by each cycle. After completion of phase I, all patients, that are treated with a dose below the determined MTD, can be dose escalated at the discretion of the investigator [39, 41].

After establishing MTD in phase I, accrual continues in phase II to evaluate the efficacy and safety of the combination therapy. A total of 41 evaluable patients will be included (patients enrolled in the phase I part within the conventional dose escalation phase at the dose level considered as the MTD may be included).

All subjects will continue on study drugs until disease progression, unacceptable toxicity or treatment discontinuation for any other reason, respectively.

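### The phase I moderate-toxicity tier is capped at exact grades, so some worse events that miss the qualified DLT list count for nothing although a milder grade of the same event counts

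*Protocol article*

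**What the plan says.** The Study design section sets two tiers of cycle 1 toxicity. DLTs are introduced as "drug related adverse events preventing the administration of the drug combination" and then defined by a list. Grade 3 or 4 non-hematologic toxicity is on the list, with alopecia, nausea, emesis and diarrhea taken out. The last three come back only under a condition: "grade 3 or greater nausea and/or emesis despite the use of optimal anti-emetic prophylaxis" and "grade 3 or greater diarrhea that occurs despite maximal supportive therapy". The blood-related entries are "neutropenia grade 4 for more than 7 days", "febrile neutropenia grade 3", and thrombocytopenia at grade 4 or at grade 3 with bleeding. Anemia and lymphopenia have no entry.

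The lower tier reads: "Moderate toxicities are defined as any grade 2 non-hematologic toxicity excluding alopecia, or any grade 3 hematologic toxicity".

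Both tiers drive dose decisions. One DLT or three moderate toxicities in cycle 1 ends the single-patient cohorts (Study design; repeated under Determination of sample size). After Table 1, the maximum-administered dose (MAD) is the dose at which "DLT or 3 moderate toxicities occur in at least two of six patients treated at that dose level", and "Determination of MAD and MTD is based on DLT or 3 moderate toxicities observed during the first treatment cycle".

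**The concern.** A toxicity score used for dose escalation should never fall as an event gets worse. Here it can. The moderate tier stops at one exact grade, and the DLT tier does not always begin at the next grade, because some of its entries need a further condition. An event above the moderate grade that fails the condition is scored nowhere.

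The score decides when single-patient escalation ends and which dose is called the MAD or MTD, and the MTD is the dose carried into phase II. In the accelerated phase one patient's score settles the matter. Measured against open-ended grades, the rule as written can only under-count toxicity.

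**Working it through.** **The plan's own figure.** Determination of sample size gives a power above 87% to see at least one of three patients with a trigger when its probability is 50%. This reproduces: 1 − 0.5³ = 0.875. It does not depend on how the tiers are worded, so it neither supports nor weakens this point.

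**Scoring each event by the text.**

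| Cycle 1 event | Milder grade | Worse grade | Rests on |
|---|---|---|---|
| Nausea or emesis, prophylaxis not optimal | 2: moderate | 3 or above: neither | text alone |
| Diarrhea, support not yet maximal | 2: moderate | 3 or above: neither | text alone |
| Neutropenia, grade 4 for 7 days or less | 3: moderate | 4: neither | worst-grade scoring |
| Anemia, lymphopenia | 3: moderate | 4: neither | worst-grade scoring |
| Febrile neutropenia, neutropenia 7 days or less | 3: DLT | 4: neither | worst-grade scoring and hematologic class |
| Thrombocytopenia | 3: moderate (DLT if bleeding) | 4: DLT | no gap |
| Other non-hematologic, except alopecia | 2: moderate | 3 or 4: DLT; 5: not named | capped DLT entry |

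For nausea, emesis and diarrhea the comparison is with grade 2. Grades 3 and 4 are both unscored when the condition is not met.

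**Does other text close the gap?** The intra-patient escalation rule, from cycle 2, requires non-hematologic toxicity of grade 1 or less. A patient with grade 3 diarrhea could therefore not be escalated herself. But the protocol calls that rule separate from the dose-escalation design, so it does not supply the missing score.

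**When the decision changes.** Count per patient, as the MAD rule does. Take a patient with no DLT, k scored moderate toxicities and g unscored gap events.

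- Text as written: triggers if k ≥ 3.
- Open-ended tier: triggers if k + g ≥ 3.

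With k and g each from 0 to 3 there are 16 combinations. The two rules differ in six: (k, g) = (0,3), (1,2), (1,3), (2,1), (2,2), (2,3). They agree in the other 10. These are rule outcomes, not probabilities.

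- Two moderate toxicities plus grade 2 diarrhea: 2 + 1 = 3, triggers. The same two plus grade 3 diarrhea before maximal support: 2, does not.
- Two moderate toxicities plus grade 3 neutropenia: 3, triggers. The same two plus grade 4 neutropenia for 6 days: 2 on worst-grade scoring, does not.
- One gap event with k = 0 or 1 changes nothing.

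At a six-patient level, one such patient matters only if she moves the count across the limit: 2 of 6 is the MAD, 1 of 6 is within the MTD limit.

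**Are these event types plausible here?** The rationale for the combination names six leading grade 3–4 toxicities of the bortezomib–carboplatin regimens. Five (neutropenia, lymphocytopenia, diarrhea, nausea, vomiting) are types with a possible gap; thrombocytopenia is not. Those figures pool grades 3 and 4, include a third drug, and give no split by duration or supportive care.

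**The case against.** The case against has four parts.

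1. *Keeping poorly supported nausea, emesis and diarrhea out of the DLT tier is deliberate*, because these events reflect supportive care as well as dose. That is reasonable, but it does not explain why grade 2 should count as moderate and grade 3 as nothing.

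2. *The blood-count cases depend on a convention.* A count that reaches grade 4 has normally passed through grade 3, and if every grade passed through is scored, the gap shrinks, chiefly for blood counts. This stands. The article does not state the convention, and the full protocol may. Those cases are therefore conditional.

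3. *The opening DLT sentence covers the rest.* The text goes on to define such toxicities by the list, which makes the list operative. If the opening sentence had force of its own, the gap would shrink to events that did not prevent dosing, but would not vanish.

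4. *No consequence is shown.* This stands as to size. A reader might infer that the MTD will be set too high, or that the share of leading toxicities with a gap measures how often it bites. The documents support neither: they give no rate for unsupported nausea, emesis or diarrhea, none for short grade 4 neutropenia, and none for how often these accompany two other moderate toxicities. Pass probabilities for a 3 + 3 cohort could be computed only from an assumed rate.

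The febrile neutropenia case carries the most conditions. It needs worst-grade scoring, a hematologic classification, neutropenia of 7 days or less, and no accompanying event that is itself a DLT. It should not carry the argument, though there a single event would decide.

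**Conclusion.** The point holds in a limited form. For nausea, emesis and diarrhea the inversion follows from the wording itself, for events scored at the grade reached. For short grade 4 neutropenia and for grade 4 anemia or lymphopenia it holds only under worst-grade scoring. Two DLT entries, the general non-hematologic one and febrile neutropenia, are capped where neighboring entries are open-ended.

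The moderate-tier gap has a defined reach: a DLT-free patient whose unscored events would complete three moderate toxicities and, at a six-patient level, one who moves the count across the limit. This assumes a per-patient count in the accelerated phase as well. Frequency and effect on the MTD cannot be derived from the document. It is a fault in a stated rule, not a detail left out of an article. It is worth correcting because the correction is cheap and errs toward safety.

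**What to change.** In the moderate tier, add *or greater* after each of the two grades, keep the alopecia exclusion, and limit the tier to events *not meeting a DLT criterion*. In the DLT list, change the general non-hematologic entry from grade 3 or 4 to *grade 3 or greater*, with its present exclusions, and febrile neutropenia to *grade 3 or greater*.

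The DLT changes must accompany the first. Otherwise the new tier would score a grade 5 non-hematologic event, or a grade 4 febrile neutropenia classed as hematologic, as one moderate toxicity while a lower grade is a DLT.

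Apply the wording to dose decisions from the amendment on. Enrollment has been open since November 2016, so for phase I patients already treated, check only whether the new wording would have changed a past escalation or MTD decision. The planned maximum of 24 dose-escalation patients bounds that check. Wholesale rescoring is not needed.

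The cost is a few words of protocol text. The downside is that the accelerated phase may end, or a level be declared the MAD, slightly earlier in some courses.

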**Fig. 1 Fig1:**
[figure not shown]
Accelerated titration design of the phase I part of the trial. Illustration of the accelerated titration design of the phase I part of the trial. Each box outlined in bold represents a cohort containing the indicated number of patients treated at a given dose level. Ixazomib will be administrated orally on days 1, 8, and 15 and carboplatin intravenously on days 1, 8, and 15 of a 4-week cycle. Drug dosages per dose level are given on the left side of the graph. DLT = dose-limiting toxicity; AUC = area under the curve

**Table 1 Tab1:** Drug dosages per dose level

Dose level	Ixazomib orally on days 1, 8, 15 every 4 weeks	Carboplatin i.v. on days 1,8 and 15 every 4 weeks
1	3 mg	AUC 1.5
2	3 mg	AUC 2
3	4 mg	AUC 2
4	4 mg	AUC 2.5

AUC = area under the curve

The maximum-administered dose (MAD) is defined as the dose at which DLT or 3 moderate toxicities occur in at least two of six patients treated at that dose level. The dose-level just below the MAD is considered the maximum-tolerated dose (MTD), providing that DLT or 3 moderate toxicities are observed in fewer than two of six treated patients (or fewer than one third if more than six patients will be treated) at that dose level. Determination of MAD and MTD is based on DLT or 3 moderate toxicities observed during the first treatment cycle.

Beginning with the 2nd cycle an intra-patient dose escalation is allowed. This is separate from the alternate dose escalation design of the phase I part. If the nadir ANC was ≥500/mL, the nadir platelet count ≥50,000/mL, and non-hematologic toxicities were grade ≤ 1 in the previous cycle, the current dose level can be escalated by one dose level by each cycle. After completion of phase I, all patients, that are treated with a dose below the determined MTD, can be dose escalated at the discretion of the investigator [39, 41].

After establishing MTD in phase I, accrual continues in phase II to evaluate the efficacy and safety of the combination therapy. A total of 41 evaluable patients will be included (patients enrolled in the phase I part within the conventional dose escalation phase at the dose level considered as the MTD may be included).

All subjects will continue on study drugs until disease progression, unacceptable toxicity or treatment discontinuation for any other reason, respectively.

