### Study population

Overall, a maximum of 53 patients will be included. Of them, a maximum of 24 will be treated in the dose escalation phase and 41 patients in the phase II part of the study.

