### Patients

Patients with metastatic histologically confirmed triple-negative adenocarcinoma of the breast will be assessed for eligibility. Detailed inclusion and exclusion criteria are listed in Table 2. Patients with locally advanced disease are eligible provided they cannot be offered a potentially curative loco-regional treatment option. TNBC is defined by the absence of staining for estrogen receptor (IHC < 1%), progesterone receptor (IHC < 1%) and HER2/neu (IHC 1+ or ISH ratio of < 2.0 between HER2 gene copy number and centromere of chromosome 17 or a copy number of 4 or less [42]). A signed informed consent, with the understanding that consent may be withdrawn at any time without prejudice to future medical care, have to be provided prior to any study-specific procedure. All patients must be female and aged 18 or older with a performance status of ECOG 0–2 and a life expectancy of at least 12 weeks. A disease progression with at least one measurable lesion according to RECIST 1.1 criteria must be documented. Patients must be pretreated with at least one prior line of chemotherapy for advanced disease or a progression must have occurred within 12 months of completion of adjuvant chemotherapy. Women of childbearing potential must have a negative pregnancy test at screening and agree to practice 2 effective methods of contraception, at the same time. An adequate left ventricular ejection fraction at baseline, defined as LVEF ≥50% by either echocardiogram or MUGA and adequate hematological, liver and renal function (absolute neutrophil count ≥1.5 × 10^9^/L, hemoglobin ≥8 g/dL, platelets ≥100 × 10^9^/L, albumin ≥2.5 g/dL, serum bilirubin ≤2 mg/dL, aspartate transaminase and alanine transaminase ≤3 x ULN without liver metastases and ≤ 5 x ULN with documented liver metastases, and serum creatinine ≤1.5 mg/dL or calculated creatinine clearance ≥50 ml/min) is required. If present, a peripheral neuropathy must be less or equal to grade 1 or grade 2 without pain.

**Table 2 Tab2:** Detailed Inclusion and Exclusion criteria

Inclusion criteria	Exclusion criteria

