## Discussion

Inhibition of DNA repair mechanisms by proteasome inhibitors could sensitize triple-negative breast tumors to DNA damaging agents like platinum salts. Within the AGMT MBC-10 trial we utilize an innovative straight forward trial concept supporting an expedite early development for the drug combination of ixazomib and carboplatin for the treatment of TNBC. For both, carboplatin and ixazomib, the single agent maximum tolerable dose (MTD) is already known. In order to reduce the number of patients treated at sub-effective doses we use an accelerated titration design in which a single patient will be enrolled per dose level [39]. If toxicities during cycle 1 are outside the predefined acceptable range, or dose level 4 have been reached, the cohort is expanded to three patients and dose escalation reverts to a conventional 3 + 3 design. During the phase I part of the trial, an intra-patient dose escalation will provide the individual patient with a higher chance to reach effective drug dosages. Such escalation is allowed beginning with cycle 2 if toxicities in the previous cycles were within a predefined range [39, 41]. After determining the MTD, patient enrollment will seamless continue into the phase II part of the trial without any delay due to regulatory issues. This trial is accompanied by a translational research program, aimed to identify a subgroup of patients benefiting most within this heterogeneous disease and to decipher resistance mechanisms to this novel drug combination.

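### The nadir blood-count limits for intra-patient dose escalation are printed per mL, a 1,000-fold unit error that leaves the haematologic check with practically no effect

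*Protocol article*

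**What the plan says.** The rule for raising an individual patient's dose from cycle 2 onward is in the protocol article, Methods, Study design, below Table 1. Its blood-count conditions are: "If the nadir ANC was ≥500/mL, the nadir platelet count ≥50,000/mL". The rest of the sentence gives the third condition and the permitted step: "non-hematologic toxicities were grade ≤ 1 in the previous cycle, the current dose level can be escalated by one dose level by each cycle".

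The Discussion describes the purpose of the rule: "Such escalation is allowed beginning with cycle 2 if toxicities in the previous cycles were within a predefined range". The nadir limits appear only once in the article and in no other unit.

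Elsewhere the article reports the same two counts per litre. The eligibility limits in Methods, Patients, are "absolute neutrophil count ≥1.5 × 10^9^/L" and "platelets ≥100 × 10^9^/L".

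The haematologic dose-limiting toxicities (Methods, Study design) are "neutropenia grade 4 for more than 7 days, febrile neutropenia grade 3, thrombocytopenia grade 4, or thrombocytopenia grade 3 with bleeding".

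**The concern.** A nadir limit is meant to separate patients whose marrow has tolerated the current dose from those whose marrow has not. A limit of 500 neutrophils per mL is half a neutrophil per µL, and 50,000 platelets per mL is 50 per µL. Only a patient with essentially no neutrophils or platelets would fall below such limits, so as printed they do not separate anyone.

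This matters because marrow toxicity is the main toxicity to expect. The Background says carboplatin is more haematotoxic than cisplatin. It also reports grade 3 and 4 thrombocytopenia in 63% and 58% of patients in two trials that added a third drug to bortezomib and carboplatin, and neutropenia of those grades in 52% in one of them. Two of the three escalation steps in Table 1 (level 1 to 2 and level 3 to 4) raise the carboplatin dose. The remaining condition in the rule covers non-haematologic toxicity only and gives no protection here.

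**Working it through.** **Inputs, all from the protocol article**

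- Printed nadir limits: ANC 500/mL, platelets 50,000/mL (Study design, below Table 1).
- Eligibility limits: ANC 1.5 × 10^9/L, platelets 100 × 10^9/L (Patients; repeated in Table 2).
- Conversion: 1 L = 10^3 mL = 10^6 µL.

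**Step 1. Convert the limits as printed**

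- ANC: 500/mL × 10^3 mL/L = 5 × 10^5/L = 0.0005 × 10^9/L.
- Platelets: 50,000/mL × 10^3 mL/L = 5 × 10^7/L = 0.05 × 10^9/L.

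**Step 2. Convert the same digits read per µL**

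- ANC: 500/µL × 10^6 µL/L = 5 × 10^8/L = 0.5 × 10^9/L.
- Platelets: 50,000/µL × 10^6 µL/L = 5 × 10^10/L = 50 × 10^9/L.

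**Step 3. Compare both readings with the eligibility limits**

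| Count | Eligibility (10^9/L) | Nadir limit per mL (10^9/L) | Eligibility ÷ limit | Nadir limit per µL (10^9/L) | Eligibility ÷ limit |
|---|---|---|---|---|---|
| ANC | 1.5 | 0.0005 | 3,000 | 0.5 | 3 |
| Platelets | 100 | 0.05 | 2,000 | 50 | 2 |

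Read per µL, the limits are one third and one half of the counts needed to enter the trial, which is a sensible place for a nadir limit. Read per mL, they are thousands of times lower. The two readings differ by the same factor for both counts: 0.5/0.0005 = 50/0.05 = 1,000.

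**Step 4. See who passes the printed limits**

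Take nadirs at one fifth of the likely intended limits.

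- ANC 0.1 × 10^9/L = 100,000/mL, and 100,000/500 = 200.
- Platelets 10 × 10^9/L = 10,000,000/mL, and 10,000,000/50,000 = 200.

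Both counts exceed the printed limits 200-fold, although both fail the likely intended limits.

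**Step 5. See whether the DLT definition fills the gap**

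It does so only in part. Grade 4 neutropenia counts as a DLT only when it lasts more than 7 days, and grade 3 thrombocytopenia only when there is bleeding. For a patient with shorter grade 4 neutropenia, or with grade 3 thrombocytopenia without bleeding, the nadir limits are the only numeric haematologic condition stated for escalation. The article also describes intra-patient escalation as separate from the cohort escalation design.

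**The case against.** The strongest reply is that this is a one-character slip with little practical effect.

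- **The intended values are easy to guess.** The article's own eligibility scale points to per µL, and clinicians would probably recognise the limits. This lowers the likelihood of harm, but the printed threshold is still wrong.
- **The PDF reading may have turned µ into m.** This cannot be fully excluded, since µ appears nowhere else in the text and its rendering cannot be checked. The symbols α, β, ≥ and × did survive, which makes it less likely. A look at the published page would settle it.
- **A DLT would block escalation anyway.** The article defines DLTs as events that prevent giving the combination, and escalation is permitted, never required. A patient with grade 4 thrombocytopenia is therefore an unlikely candidate for a higher dose, even though that patient would pass the printed count limits. This argument stands for DLTs. It does not reach the non-DLT cytopenias in Step 5 of the working.
- **Few patients are exposed.** The cap is 24 ("a maximum of 24 will be treated in the dose escalation phase"), and Table 1 lists no level above 4. If accelerated titration runs to level 4 without a trigger, levels 1 to 3 hold one patient each, so about three patients start below the top level. More are possible if the 3 + 3 phase begins earlier. The figure of 24 is a ceiling and not an estimate.
- **Sites dose from the full protocol.** That document is not available here and may be correct. The finding is therefore about the text at hand, and the remedy includes a check of the source.

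These points limit the consequences. None of them makes the printed limits correct.

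**Conclusion.** The concern holds. Both nadir limits for intra-patient dose escalation carry a unit that is wrong by a factor of 1,000, and as printed the blood-count part of the rule excludes practically no one. This should be fixed, because it is a stated threshold for giving a patient a higher dose.

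The reach is limited. The non-haematologic condition and the stop for unacceptable toxicity remain in force. The rule applies to phase I, where at most 24 patients enter dose escalation and probably far fewer could use it. The MAD and MTD rest on cycle 1, while this rule starts with cycle 2, so they are unaffected, as are sample size, alpha and power.

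The conversion and the factor of 1,000 rest on the printed text alone. Two assumptions remain: that the text at hand reproduces the published unit correctly, and that per µL was intended. The second is an inference from the eligibility scale, well supported but not stated in the article.

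**What to change.** Check the two limits against the full protocol and restate them on the 10^9/L scale already used for eligibility: most likely nadir ANC ≥0.5 × 10^9/L and nadir platelets ≥50 × 10^9/L, that is 500/µL and 50,000/µL. Confirm that the documents used at the sites carry these values. If the full protocol also prints per mL, correct it there and check the blood counts of any patient already escalated within the trial.

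The cost is a one-line correction and a check of the site documents. Design, sample size and analysis do not change.
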